The goals of the Synuclein-Quantification (Syn-Q) study are to (1) define rates of cutaneous P-SYN detection across a well-characterized group of patients with either prodromal iRBD or PD across a range of severities, (2) quantify the amount P-SYN detected from each of three biopsies to define the topographical distribution and, (3) measure rates of P-SYN change over time. Successful completion of this study will establish a foundational understanding of the natural progression of cutaneous P-SYN in patients with established or prodromal PD.

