#### Exclusion criteria for all subjects

Any history of a prior negative test for synuclein pathology in cerebrospinal fluid or skin.Clinical evidence of severe vascular disease (history of ulceration, poor wound healing, vascular claudication).History of allergic reaction to local anesthesia needed for skin biopsies.Use of blood thinners (aspirin or Plavix alone is allowed).Significantly impaired wound healing, history of scarring or keloid formation.Concurrently enrolled in a disease-modifying clinical trial.

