A recent report of the c-ABL kinase inhibitor, risvodetinib, in 137 patients with untreated PD has shown the potential utility of skin biopsy to quantify P-SYN over time (30). Patients were treated with 50 mg, 100 mg, or 200 mg daily doses of risvodetinib and cutaneous P-SYN was measured at baseline and 12 weeks after treatment. There were dose-dependent reductions in quantitative measures of P-SYN where reduced P-SYN was detected in 30%, 60%, and 64% of patients treated with the 50 mg, 100 mg or 200 mg doses, respectively. Although preliminary, the data strongly support the need for additional longitudinal studies to understand the natural history of peripheral P-SYN accumulation. The study also demonstrates that skin biopsy quantitation of P-SYN may be capable of detecting therapeutic changes with pharmacologic interventions. Although limited data on the use of this AI-supported P-SYN quantitation system exists, the existing study will provide direct comparison of the digital results with the direct pathologist review of the glass slides, offering an important step in the validation of this software. There are limitations to the current study. Healthy and disease control subjects are not included in this study. Numerous other studies have included both healthy and disease controls, and were considered outside of the scope of this project, given the very low rates of P-SYN detection in those populations. The duration of follow-up is limited to 18 months. If study funding can be extended, further follow-up will be considered. Finally, other synuclein biomarkers are not being tested in parallel.

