## Conclusion

Despite the limitations, this will be the first prospective, blinded, natural history study of quantitative P-SYN measurement in patients with established and prodromal PD. The findings from this study could support real-time monitoring tools for Parkinson’s progression and offer significant advantages as ongoing trials with anti-synuclein therapies which currently lack a method to measure P-SYN in humans. In addition, the use of AI-enhanced pathological quantitation of P-SYN offers a scalable tool appropriate for larger volumes of testing.

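### The exclusion list bars only concurrent enrolment in a disease-modifying trial, so people recently given a P-SYN-lowering agent can enter a cohort meant to show the natural rate of change

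*Protocol article*

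**What the plan says.** In the protocol article, the section on exclusion criteria for all subjects has one item on disease-modifying treatment: "Concurrently enrolled in a disease-modifying clinical trial". It gives no look-back period and does not mention treatment that has already ended.

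The aim is described as an untreated course. The Introduction says: "Successful completion of this study will establish a foundational understanding of the natural progression of cutaneous P-SYN". The Conclusion says that "this will be the first prospective, blinded, natural history study of quantitative P-SYN measurement".

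The Discussion summarises a trial of an investigational c-ABL kinase inhibitor in 137 patients with untreated PD, in which "cutaneous P-SYN was measured at baseline and 12 weeks after treatment". It reports: "There were dose-dependent reductions in quantitative measures of P-SYN where reduced P-SYN was detected in 30%, 60%, and 64% of patients", by increasing dose. The article itself treats this evidence as early: "Although preliminary, the data strongly support the need for additional longitudinal studies to understand the natural history of peripheral P-SYN accumulation".

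The list of visit procedures includes a review of history and current medications and the collection of three years of medical records. The key covariates named under Statistical considerations are sex, cognitive scores, disease duration, UPDRS Parts 2 and 3, and autonomic nerve fibre density. Exposure to disease-modifying treatment is not named.

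**The concern.** A natural-history rate is useful as a reference only if the people who supply it were not under the influence of a treatment that moves the outcome. By barring concurrent trial enrolment, the authors acknowledge that risk. The same reasoning applies to someone whose treatment ended just before baseline, and the printed wording does not reach that person.

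The article supplies the reason to care. It reports that an agent was followed by lower P-SYN within 12 weeks, and its Conclusion refers to anti-synuclein trials now under way. The Objectives section intends the results to support P-SYN as a marker of response in disease-modifying trials, so a distorted rate would pass into the planning of those trials.

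The distortion could go either way. If P-SYN recovers after treatment, a lowered baseline makes the later increase look too steep. If the effect lasts, the increase looks too shallow.

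**Working it through.** **Inputs from the protocol article**

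- Planned increase: 16% over 12 months in all four groups (Sample size justification).
- Hypothesis: more than 10% per year in PD (Expected outcomes).
- Enrolment: 100 in total, 25 per group (Study design and cohort).
- Losses: 10% dropout per year and 5–10% biopsy-negative (Sample size justification).

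**The plan's own rate.** From the Table 1 means, with 5 years per Hoehn and Yahr stage:

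- Stage 1 to 2: (4.6/1.9)^(1/5) − 1 = 19.3% per year
- Stage 2 to 3: (7.9/4.6)^(1/5) − 1 = 11.4% per year
- Stage 1 to 3: (7.9/1.9)^(1/10) − 1 = 15.3% per year

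The plan's figure of about 16% is therefore roughly recovered. I use it only as the benchmark for untreated participants.

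**Evaluable numbers at 12 months**, taking the upper biopsy-negative figure:

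- Pooled: 100 × 0.90 × 0.90 = 81
- Per group: 25 × 0.90 × 0.90 = 20.25, about 20

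**Effect of prior exposure.** Let f be the share recently treated and c their apparent 12-month change. With each person weighted equally,

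observed mean = (1 − f) × 16% + f × c.

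The documents give neither f nor c. Two contrasting assumptions show the range:

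- *Flat:* no change after treatment, so c = 0.
- *Full recovery:* baseline is suppressed by s and returns to the untreated path within 12 months, so c = 1.16/(1 − s) − 1. This gives 28.9%, 45.0% and 65.7% for s = 10%, 20% and 30%.

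| f | Flat | s = 10% | s = 20% | s = 30% |
|---|---|---|---|---|
| 1% | 15.84% | 16.13% | 16.29% | 16.50% |
| 2% | 15.68% | 16.26% | 16.58% | 16.99% |
| 5% | 15.20% | 16.64% | 17.45% | 18.49% |

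Example for f = 5%, s = 30%: 0.95 × 16% + 0.05 × 65.7% = 15.20% + 3.29% = 18.49%.

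**Reading the table**

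- In the pooled cohort, 1–2% of 81 is about one or two people. The shift runs from −0.32 to +0.99 points.
- In a single group, one exposed person among 20 is 5%. The shift runs from −0.80 to +2.49 points.
- None of these cases brings the mean below the hypothesised 10%.

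**The case against.** The strongest reply is that this is a matter of eligibility preference, with no contradiction and no wrong figure. An article condenses its protocol, and the full document may contain a washout rule. The evidence on the agent is preliminary: it is given as shares of patients with reduced P-SYN, without a mean reduction, a comparator or a course after treatment. The one trial described enrolled untreated PD, while this study also admits people on levodopa or deep brain stimulation, so the overlap in populations is not established. Most of this stands and limits the size of the point. It does not remove it, because the criterion is printed and its scope is expressly concurrent.

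Three stronger readings are tempting and are not supported:

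- *That the plan permits joining a disease-modifying trial midway through follow-up.* Being enrolled concurrently most naturally means at any time during the 18 months, and a review of the inclusion and exclusion criteria is listed among the visit procedures. How biopsies taken after a breach are handled is ordinary content for the full protocol or SAP.
- *That the bias is large, or has a known sign.* No exposure share or mean effect is given. Recovery after treatment is an assumption in the working above, not a documented fact.
- *That exposure could not be disentangled later.* Medication review and three years of records are already collected, so exposed people can probably be identified.

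**Conclusion.** The point holds in a limited form. As printed, the criterion admits people who recently received an investigational P-SYN-lowering agent into a study whose main product is the natural rate of P-SYN change, and the analysis section does not name exposure as a covariate. The size and direction of the bias cannot be determined from the documents. With an assumed 1–2% exposed, the pooled 12-month figure moves by about 1 point or less. One exposed person in a group of about 20 evaluable could matter more, because the plan also promises inference within each of the four groups. These figures rest on the assumed f and c, on equal weighting of participants, and on the planned 16% being right for untreated people. This is a modest design weakness that does not threaten the study, but it deserves correction because the remedy is simple.

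**What to change.** Reword the exclusion criterion to cover concurrent or recent receipt of investigational disease-modifying treatment, and state that it applies throughout follow-up. The length of the look-back is for the sponsor to set.

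If recruitment is already closed, leave eligibility alone and do two things:

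- Flag prior or new exposure, with dates, from the medication review and the three-year records.
- Before database lock, when unblinding takes place, specify a natural-history estimate that leaves out exposed participants' affected biopsies, and report it alongside the estimate from all biopsies.

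The cost is a short amendment to one criterion or, failing that, one data field and one sentence of analysis. A few candidates or biopsies would be lost from that estimate.

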### Study visits and participant data collection

#### Trial synopsis

Approximately 25 sites will participate in recruiting 75 individuals diagnosed with Parkinson’s disease and 25 patients with iRBD in an 18-month longitudinal study where skin biopsies will be performed at 3 sites on each patient at 6-month intervals (baseline, 6, 12, and 18 months). Detailed quantified neurological examination, cognitive evaluation, medical history, and questionnaires will be performed at each visit. Additional biomarkers, imaging, and clinical information (if available) will be obtained for the purpose of determining disease progression for PD cohort and phenoconversion to clinically apparent synucleinopathy for the iRBD cohort. All testing will be repeated at all visits to define any changes to clinical diagnosis (clinical phenoconversion or progression). Skin biopsies will be repeated at the 6- and 12- and 18-month follow-up visits to determine the rate of P-SYN accumulation over time and the rates of nerve fiber degeneration within punch skin biopsies.

Study visit will include

Review of enrollment forms (inclusion and exclusion criteria).Informed consent.Review of medical history and current medications.Quantified neurologic examinations: All participants will have standardized neurologic examinations using published methods. The neurological examinations will be performed by the treating physicians. The specific examinations will include:

a MDS-UPDRS (Parts I, II, III & IV) (18).

Part III motor assessments will be performed in the “OFF” state, preferably with the last dose of Levodopa taken the night before. After conducting the MDS-UPDRS Part III, medication can be taken. (In order to reduce ‘OFF’ time for the participant, it is suggested that the MDS-UPDRS part III should be conducted as soon after consent as possible). The remainder of study visit would be conducted while patient is in the “ON” state. For those participants who are being treated with Deep Brain Stimulation, the stimulation will be turned off for the MDS-UPDRS part III assessment.

b Hoehn and Yahr scores.

5 Smell Testing: All subjects will complete the University of Pittsburgh Brief Smell Identification Test (BSIT) a 12-item, self-administered scratch and sniff test designed to measure olfactory function (19).6 Orthostatic vitals to be measured with the participant supine after 5 min and then standing after 3 min.7 Blood Plasma collection:

c One 4 mL EDTA tube for genetic testing for inherited forms of PD (LRRK2, GBA1, PRKN, PINK1, and SNCA) which is collected at the baseline visit only.d One 10 mL EDTA tube collected at all visits for blood-based biomarkers (plasma p-tau-217, neurofilament light chain, glial fibrillary acidic protein). as exploratory outcomes.

8 Three millimeter diameter and 3–4 millimeter depth punch skin biopsies taken from the posterior cervical area 3 cm lateral to the C-7 spinous process, distal thigh 10 cm above the lateral knee, and distal leg 10 cm above the lateral malleolus after local analgesia with 1% lidocaine (9).9 Cognitive/Neurological Testing and Questionnaires: All participants will complete the following questionnaires/assessments:

e European Quality of Life Instrument (EQ-5D & VAS) (20)f SLUMS cognitive assessmentg Parkinson’s Disease Questionnaire-39 (PDQ-39) (21)h Orthostatic Hypotension Questionnaire (OHQ) (22)i REM sleep behavior disorder questionnaire (RBDSQ)j Scales for Outcomes in Parkinson’s Disease-Autonomic (SCOPA-AUT)k Geriatric Depression Scale-short form (GDS)

10 Collection of medical records for the last 3 years including any imaging (DaTscan, MRI, PET, SPECT, neurologic testing or genetic testing)

All assessments and blood collection will be repeated once every 6 months, with the exception of genetic testing which takes place only once at the baseline visit.

### Standardization of data and tissue collection

To minimize potential variability in study outcomes, all tissue and clinical data will be obtained using standard methods that we have utilized in multiple prior studies (10, 23).

#### Skin biopsy samples

Punch skin biopsies 3 mm in diameter and 3–4 mm in depth will be taken from all subjects at the distal leg 10 cm above the lateral malleolus, the distal thigh 10 cm above the lateral knee, and the posterior cervical region 3 cm lateral to the C-7 spinous process. Biopsy locations are selected based on prior publications that demonstrate differential phosphorylated alpha-synuclein deposition in proximal and distal locations across the different synucleinopathies (24, 25). The Brain-First, Body-First theory of P-SYN deposition would suggest that patients with RBD prior to other manifestations of PD might have greater distal P-SYN deposition (26). The three sites we have selected provide maximal sensitivity and specificity across all synucleinopathies (9). Local analgesia will be provided using lidocaine with epinephrine (1:100,000). Skin biopsy samples do not require sutures, and band aids will be provided for wound care. Skin biopsy specimens will be fixed in Zamboni paraformaldehyde solution in pre-labeled tubes, placed into a standard shipping pack, and shipped overnight for central processing. At the central processing site, biopsies will be washed and placed in a 20% glycerol cryoprotectant solution.

#### Skin biopsy processing and immunostaining

After storage in cryoprotectant solution for at least 24 h, skin samples will then be sectioned into 50 μm thick samples using a cryostat. Tissue will be immunostained with antibodies against protein gene product 9.5 (PGP9.5: a pan-axonal marker to identify nerve fibers) and with antibodies to phosphorylated alpha-synuclein using free-floating sections in our standard protocols. Six skin biopsy specimens from each biopsy will be dual immunostained with rabbit anti-protein gene product 9.5 (Cederlane: 1:1,000) and phosphorylated alpha-synuclein (Wako: 1:1,000), mounted on glass slides as previously reported (9). An immunofluorescent microscope will perform an initial review of slide quality. In all experiments, positive and negative controls are run to confirm the results.

#### Biopsy analysis

All biopsies will be evaluated in a blinded fashion using standard protocols with slides randomly intermixed with other blinded studies to maintain data integrity (27). Cutaneous axons are identified by the antibody binding to protein gene product 9.5. Nerve fiber subtypes are defined by their pathological characteristics within dermal substructures, including sudomotor (sweat gland) fibers, pilomotor fibers (within piloarrector muscles), vasomotor nerve fibers surrounding blod vessels, nerve bundles, intra-epidermal nerve fibers and the subepidermal plexus (28). Pathologist reading will include a semi-quantitative analysis of each biopsy site. This reading includes the number of positive cutaneous dermal structures for each tissue section for each biopsy and also accounts for the intensity of P-SYN staining (29). All slides will also undergo complete digitization (VS200, Evident). A series of optical images will be acquired at 2 μm intervals through the depth of the section as a Z-stack (VS200, Evident). A custom-developed digital image analysis package (NerValence, CND Life Sciences) integrated with Oncotopix software (Visiopharm, Hørsholm, Denmark; Version 2023.09.3.15043) was designed and optimized specifically for objective identification and quantification of cutaneous nerve fibers and phosphorylated alpha-synuclein (P-SYN) deposits within digitized immunofluorescent slide images. This artificial-intelligence (AI) augmented algorithm will be used to detect and quantify cutaneous intra-axonal P-SYN deposits (30).

Quantitation of P-SYN (um^2^ of P-SYN per mm^2^ of tissue analyzed) will be reported for each biopsy specimen. The amount of P-SYN will be noted for each cutaneous dermal sub-structure (blood vessels, nerve bundles, pilo-arrector muscles, sweat glands, and sub-epidermal plexus) as previously reported (23). Intra-epidermal nerve fiber density (IENFD) will be calculated using standard methodology for immunostained nerve fibers, reported as nerve fibers/millimeter (31). Pathological review and grading of P-SYN deposition for all tissue sections will follow strict blinding measures, including slide randomization, random number generation, and blinding between pathology reviewers and study staff (9). Results of the AI-generated data will be reviewed against pathologist confirmed results in all biopsies.

#### Definition of “positive biopsy results”

Only biopsies expressing P-SYN co-localized within a peripheral nerve axon (confirmed using immunostaining for anti-PGP9.5 and anti-P-SYN) will be considered positive. Any equivocal section will be considered negative. Any positive result indicates a positive case (e.g., if one of 3 biopsies is positive, the case is positive).

#### Clinical data capture

All study questionnaires, examination scores, and demographic information, will be acquired using electronic data capture. Ancillary data (including prior medical records, test results, and polysomnography) will be uploaded into the electronic data capture system.

### Blinding and review of data

#### Study blinding

The clinical and biopsy data will be blinded and maintained separately. Pathology slides will be randomized using numbers assigned by the Electronic Data Capture System (EDC). Blinded slides will be batch processed in combination with multiple other blinded studies to ensure all staff and pathology readings are blinded to study, visit and disease state. Unblinding will occur only at the time of database lock.

### Objectives

This is a prospective longitudinal study of individuals with PD and prodromal RBD to establish cutaneous P-SYN deposition as a stable, reliable quantitative measure that changes in parallel with disease progression. The results of this study will provide the basis for establishing cutaneous P-SYN as a biomarker of response to disease-modifying therapeutic interventions and a possible surrogate biomarker for outcomes in clinical trials of disease-modifying therapies. The primary objectives of this study are:

To determine rates and patterns of P-SYN detection in iRBD and PD across Hoehn and Yahr stages I, II and III.To measure the change quantity and pattern of cutaneous P-SYN deposition over time.To enhance pathological detection and quantitation of P-SYN using rapid, high resolution, confocal microscopy combined with a novel AI-augmented pathology protein detection system.

### Secondary objective

We predict that AI-enhanced quantitative detection of cutaneous P-SYN will provide an accurate, continuous outcome measure that will correlate with disease stage and severity. Whole slide imaging with extraction of representative neural structures, target stain detection, segmentation, stain quantification, and pattern recognition will be performed using deep learning algorithms (NerValence, CND Life Sciences). We anticipate that results will be correlated with MDS-UPDRS scores, cognitive assessments, Hoehn and Yahr Stage, and daily levodopa dose.

### Statistical analysis and blinding

#### Expected outcomes

We hypothesize that cutaneous P-SYN will increase by >10% per year in patients with PD. We will confirm our ability to quantify the deposition of P-SYN in a blinded, prospective longitudinal study of clinically defined PD patients across a range of severity and measure the change in cutaneous P-SYN at 6-month intervals over an 18-month period.

#### Statistical considerations

Descriptive statistics will be used to report all demographic information and clinical examination findings for all groups (PD stages I-III and iRBD). For continuous variables data will be reported as mean, standard deviation, median, minimum, maximum and inter-quartile range.

For the primary objectives, the presence or absence of P-SYN will be reported as a binary outcome for the first objective (detection of P-SYN). Quantitation of P-SYN will be measured as a continuous variable for the second objective (quantitation of P-SYN). We have established that a P-SYN > 0 is defined as a ‘P-SYN positive’ result and will separate groups using dichotomous measures. We will also investigate ROC curve analysis to determine if an alternative value would maximize sensitivity and specificity using continuous quantitative measurement of P-SYN. For comparisons over time, the initial biopsy results will be compared against future biopsy results using Krippendorff’s alpha reliability estimate. Reliability will be measured by quantified continuous P-SYN values between visits with the change in continuous values used to determine mean change over time. Additional endpoints will include change in disease severity over time, or phenoconversion to clinically apparent synucleinopathy (in patients with iRBD).

Data will be compared first using repeated measures Analysis of Covariance (ANCOVA), with phenoconversion/disease progression as the predictor variable. The primary dependent variable is the quantitative measure of P-SYN deposition. Other key covariates will include sex, cognitive examination scores, disease duration, UPDRS Part 2 and Part 3 total scores, and autonomic nerve fiber density (pilomotor nerve fiber density and sudomotor nerve fiber density) (32). These will be evaluated individually and together with descriptive and multivariate statistics to identify potential violations of statistical assumptions. If normality is violated, then transformations or bootstrap methods will be used. For comparisons of demographic and laboratory data within- and between groups, nonparametric tests (Kruskal–Wallis) will be used. The GEE (general estimating equation) method will be applied if the data cannot be transformed. All data will be presented as mean ± standard deviation and interquartile range using absolute values and change from baseline data for all tests of structure and function unless otherwise specified.

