## Methods

### Study design and cohort

This is a multi-center, blinded, prospective, longitudinal, observational study to evaluate phosphorylated alpha synuclein pathology in cutaneous tissues in individuals with prodromal disease (iRBD) and PD across a range of disease (Hoehn and Yahr stage I, II & III). This study aims to enroll 75 subjects diagnosed with PD with 25 subjects enrolled in each Hoehn and Yahr stage (I, II, and III), totaling 75 participants (16). Their disease state will be assessed by the International Parkinson and Movement Disorders Society Unified Parkinson’s disease rating scale (MDS-UPDRS) completed at the baseline visit. Additionally, 25 subjects diagnosed with iRBD, confirmed by polysomnogram (PSG), without evidence of PD, will be included based on their medical history. A total of 100 subjects will be enrolled. Subjects will be evaluated at baseline, 6 months, 12 months, and 18 months (+/− 30-day window).

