#### Sample size justification

Power calculations: Power analysis is based on the minimum number of subjects across the study to reach completion required for endpoint analysis of Aims 1–2. The expected dropout rate for subjects in our 2-year study is ~ 5% per 6-month period of time based on our prior natural history data in our prior studies with DLB, multiple system atrophy and Parkinson’s disease. For Aim 1, the required number needed to obtain sufficient objective pathological data (based on prior work in patients with PD and DLB) is 15 from each group (prodromal, Hoehn and Yahr stages 1, 2 and 3). Given the data in Table 1 on P-SYN values by Hoehn and Yahr stage, we estimate 5 years to move from stage 1 to 2 and 2 to 3, suggesting a ~ 16% increase in P-SYN per year. In contrast, we noted ~37% increase in P-SYN over 6 months in a prior study of dementia with Lewy bodies, consistent with an expected accelerated disease progression compared to PD. Using the data in Tables 1, 2 we expect that over 12 months we will detect a 16% increase in P-SYN across all 4 disease stages of enrollment, but with smaller absolute changes at earlier disease stages. Given the expected 10%/year dropout and 5–10% cases that are biopsy negative we require a total of 100 subjects to complete the study with > 90% power, with a 2-sided alpha of 0.05 to detect changes in P-SYN over 12 months. By increasing study duration to 18 months, we anticipate a > 90% power, with a 2-sided alpha of 0.01 to detect changes in P-SYN over 18 months in each of the 4 study subgroups (iRBD and Hoehn and Yahr stages 1–3).

**Table 1 tab1:** P-SYN quantities by H&Y staging.

Variable	H&Y Stage 1	H&Y Stage 2	H&Y Stage 3
Number	7	70	12
P-SYN (SU’s)	1.9 ± 1.3	4.6 ± 3.8	7.9 ± 5.8

**Table 2 tab2:** High sensitivity and specificity of cutaneous P-SYN detection.

Disease	Sex (M/F)	Age (± SD)	Hoehn & Yahr stage	MOCA*	P-SYN+ (#)	P-SYN+ (%)
PD	56/40	70 ± 8	2.1 ± 0.6	25.2 ± 3.7	89	92.3%
Healthy control	7/7	59.4 ± 11.1	0 ± 0	28.1 ± 1.6	4	3.3%

*MOCA, Montreal Cognitive Assessment.

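### Krippendorff's alpha between visits 6 to 18 months apart counts the expected P-SYN rise as disagreement, so it cannot isolate measurement error

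*Protocol article*

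**What the plan says.** Under Statistical considerations, the Protocol article says that for comparisons over time "the initial biopsy results will be compared against future biopsy results using Krippendorff’s alpha reliability estimate". The next sentence reads: "Reliability will be measured by quantified continuous P-SYN values between visits with the change in continuous values used to determine mean change over time".

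Study design and cohort fixes the spacing: "Subjects will be evaluated at baseline, 6 months, 12 months, and 18 months", with a 30-day window either way.

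Two other sections say what should happen between those visits. Expected outcomes states: "We hypothesize that cutaneous P-SYN will increase by >10% per year in patients with PD". Sample size justification expects that over 12 months "we will detect a 16% increase in P-SYN across all 4 disease stages of enrollment", with smaller absolute changes at earlier stages.

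The Objectives section says what the reliability claim is for: the study is to "establish cutaneous P-SYN deposition as a stable, reliable quantitative measure that changes in parallel with disease progression".

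The article gives no alpha threshold. It describes no repeat biopsy at the same visit or after a short interval, and no step that removes the time trend before alpha is calculated. It does not say whether alpha is calculated within each group or across all of them.

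**The concern.** A reliability coefficient should show how closely two measurements of the same unchanged quantity agree. Here the two measurements are a baseline biopsy and one taken at least half a year later, in a disease where the plan expects the quantity to have risen. Interval-scale alpha is 1 minus observed over expected disagreement, and every difference within a pair adds to the observed part. Assay noise, sampling of a new punch, average progression and person-to-person differences in progression all enter together.

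The Objectives section presents P-SYN as a future marker of response to disease-modifying treatment. Planners of such trials need the error of a repeat biopsy on its own, to judge how much of an observed change is real. The between-visit alpha does not give them that, and it is the only reliability statistic the article names. The review of AI output against the pathologist (Biopsy analysis) concerns agreement between methods on the same tissue, not repeatability.

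**Working it through.** **The plan's own figures.** No alpha value is stated, so there is none to reproduce. The growth rate can be checked against Table 1 with five years per stage:
- stage 1 to 2: (4.6/1.9)^(1/5) − 1 = 19.3% a year
- stage 2 to 3: (7.9/4.6)^(1/5) − 1 = 11.4% a year
- stage 1 to 3: (7.9/1.9)^(1/10) − 1 = 15.3% a year

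The plan's figure of about 16% is thus roughly recovered, and I use it below.

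**Inputs.** Table 1 mean m and SD s: 1.9 and 1.3 (stage 1), 4.6 and 3.8 (stage 2), 7.9 and 5.8 (stage 3). Growth g compounds at 16% a year: 7.7% at 6 months, 16% at 12, 24.9% at 18.

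**Error-free assay, uniform growth.** The later value is (1+g) times the first. With two visits, alpha = 1 − mean squared difference / (2 × pooled variance), which gives

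alpha = 1 − g²(m² + s²) / [s²(1 + (1+g)²) + g²m²/2].

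Stage 1 at 12 months: numerator 0.0256 × 5.30 = 0.136; denominator 1.69 × 2.3456 + 0.0256 × 3.61/2 = 4.010; alpha = 1 − 0.034 = 0.966.

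| | 6 months | 12 months | 18 months |
|---|---|---|---|
| Stage 1 | 0.991 | 0.966 | 0.926 |
| Stage 2 | 0.993 | 0.973 | 0.941 |
| Stage 3 | 0.992 | 0.969 | 0.932 |

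The correct reading for an error-free assay is 1.00, so the loss is about 0.01, 0.03 and 0.06 to 0.07. Simulation with 200,000 gamma-distributed values per stage gives the same results.

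**Assay with error (assumed shares, constant error SD).** At true within-stage reliability 0.90, simulated alpha is 0.88 to 0.89 at 12 months and 0.85 to 0.86 at 18. At 0.70 it is 0.70 to 0.71 and 0.68 to 0.70. The loss shrinks because proportional growth also widens the spread between people. At 0.50 alpha even rises slightly, to about 0.52 at 12 months.

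**Unequal individual growth (assumed).** Take a mean rise of 24% at 18 months (16% × 1.5) and a between-person SD of 24 points, with no assay error. In stage 1 the mean squared difference is 5.30 × (0.24² + 0.24²) = 0.611. Twice the pooled variance is 1.69 + (1.24² × 1.69 + 0.24² × 5.30) + 0.24² × 3.61/2 = 4.698. Alpha = 1 − 0.611/4.698 = 0.87. The same steps give 0.90 in stage 2 and 0.88 in stage 3. The documents do not give this SD.

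**If alpha were calculated across stages (not stated).** Take the three PD stages at equal size, with no true change:
- mean within-stage variance: (1.69 + 14.44 + 33.64)/3 = 16.59
- variance of the stage means about 4.8: (8.41 + 0.04 + 9.61)/3 = 6.02
- pooled alpha = 1 − (1 − r) × 16.59/22.61, where r is the within-stage reliability

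So r = 0.50 would read 0.63, and r = 0.70 would read 0.78. Adding an iRBD group, whose values are not given (1.9 ± 1.3 or 1.0 ± 1.0 assumed), gives 0.66 to 0.68 and 0.80 to 0.81.

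**The case against.** The strongest reply is that the effect is small on the plan's own numbers and that alpha is not asked to do everything. Statistical considerations assigns alpha to reliability and takes mean change from the change in values. It adds a repeated-measures analysis with GEE as a fallback, and it promises change from baseline with its SD. No decision depends on an alpha cut-off. All of this stands: the change analysis does not depend on alpha, and planners would not be left without an SD of change.

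A reader might go further than the documents allow in four ways.
- *Pooling stages inflates the planned alpha.* The article does not say that stages are pooled, and elsewhere it describes and powers the groups separately. The pooled figures are conditional.
- *A perfect assay would look mediocre.* This needs wide variation in individual progression. With an SD of 50 points, alpha would be about 0.72 to 0.76, but no passage gives such a figure. Under a normal approximation it implies that P(Z < −24/50), about 32% of people, truly lose P-SYN, which sits poorly with progressive deposition.
- *The plan expects different rates by stage.* It expects one proportional rate, with only the absolute changes differing.
- *Stability and change cannot both be shown.* They can, with separate estimates. Between-visit alpha is simply not the estimate for the first.

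What survives is narrower. The article names this statistic and this comparison explicitly, so the choice is not a detail left to a fuller document. Nothing in it separates true change from error within alpha.

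**Conclusion.** The concern holds in limited form. Between-visit alpha mixes repeat-biopsy error with the progression the study expects, and so does not measure reliability as the Objectives section needs it. With uniform growth at 16% a year and the Table 1 spread, an error-free assay loses about 0.01 at 6 months, 0.03 at 12 and 0.06 to 0.07 at 18. At reliability 0.70 the loss is about 0.02 or less. Unequal individual growth would add to the loss (0.87 to 0.90 at 18 months under the assumed SD of 24 points). Pooling stages, if done, would act in the opposite direction. A reported alpha could therefore be too low or too high, and a reader could not tell which.

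The figures are indicative only. Table 1 is in SU, whereas the endpoint in Biopsy analysis is P-SYN area per tissue area. Stages 1 and 3 rest on 7 and 12 people. The error shares are assumed, as is the gamma shape in the simulations. The analysis should be changed, but the point does not undermine the study's estimate of change.

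**What to change.** Do not use between-visit alpha as the reliability estimate. Fit a longitudinal model to the four visits that includes time, with person-specific slopes if they can be estimated. Report its within-person residual SD and ICC, by stage and biopsy site, as the measure of repeat-biopsy error. Report mean change and its SD separately. With complete follow-up, four values per person less an intercept and a slope leave two, so 25 × 2 = 50 residual degrees of freedom per stage and site before dropout.

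Repeatability across the six stained sections of each biopsy may be added, described as within-punch variation only. It does not capture the variation between one punch and the next, so it cannot replace the residual SD. If between-visit alpha is still shown, give it by stage and label it as stability that includes true change.

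The cost is revised wording and slightly more programming on data already planned; no extra biopsies are needed. One drawback remains: the residual SD will include any true change that is not linear in time, so it may overstate pure measurement error.
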